**Discussion:**

This study will provide information about hard and soft tissue dimension changes and histomorphology evaluation following ARP and natural healing in periodontally compromised molar sites, which may contribute to complement the missing information of ARP at periodontally compromised molar extraction sockets.

**Trial registration:**

Chinese Clinical Trial Register (ChiCTR) ChiCTR2200056335. Registered on February 4, 2022, Version 1.0.

## Background

Periodontitis is a chronic inflammatory condition which affects the tissues surrounding and supporting the teeth. Globally, severe periodontitis was the sixth-most prevalent health condition, affecting about 10.8% of population [1]. In recent decades, the total burden of periodontitis has increased [2], and it has become the main cause of tooth loss in adults [3]. Molar plays an important role in oral function, while it presents a challenge for periodontal treatment [4], and shows a higher risk for tooth loss due to its anatomy and position [5].

A systematic review reported that a certain amount of alveolar bone resorption occurs after natural healing, and more reduction can be expected in molar extraction sites [6]. This dimensional change of the alveolar ridge may affect the subsequent implant procedure, resulting in ridge deficiencies that can adversely impact long-term implant stability or aesthetics [7–9], necessitating additional reconstructive surgery [10, 11]. A consensus report concluded that alveolar ridge preservation (ARP) attenuated the bone resorption following tooth extraction [12]. Moreover, the indications for ARP procedures have been widening from anterior intact extraction socket to infected molar extraction sockets [13–16].

Regarding infected molar extraction, Zhao et al. [17] has confirmed that the molar extraction sockets with advanced periodontitis did resorb and change in various sites, especially at the buccal wall of the socket. Fok et al. [18] reported that prosthetically driven implants planning at first molar extraction sites due to terminal periodontitis poses greater challenge to rehabilitation, often requiring advanced augmentation procedures and sinus augmentation. Nevertheless, Kim et al. [19] revealed that ridge preservation at periodontally compromised sockets was safe and effective in reducing bone resorption. Wei et al. [20] concluded that ridge preservation could decrease the necessity of further regenerative procedures at maxillary molars with severe periodontitis during implant placement compared to natural healing sockets.

In measurement technique, most of the previous investigations usually used cone beam-computed tomography (CBCT) or peri-apical film to evaluate the change of width and height of the alveolar socket received ARP [13, 20–23]. Only a few studies reported on the three-dimensional soft tissue profile changes using intraoral scanning technique for infected molar extraction sockets [24–26].

Histological analysis is valuable in assessing and determining the clinical application of ARP, since this procedure is often related to a following dental implant therapy that requires sufficient osseointegration within genuine bone tissue [27]. Previous studies showed ridge preservation using deproteinized bovine bone mineral (DBBM) had a lower amount of new bone formation in comparison with natural healing after a follow-up period of 3–6 months [28]. Further studies with longer healing time are needed for optimizing the clinical effects of ridge preservation in periodontally compromised sockets.

Although many previous studies have confirmed the effectiveness of ARP, few studies have been conducted in periodontally compromised molar extraction sites. Soft tissues surrounding implants have significant impact on esthetics and long-term health for dental implant therapy, but the comparison between natural healing and ARP in this area is also lacking. The different histological manifestations and the effect of implant therapy for these methods are also worthy of further exploration. Therefore, this randomized controlled trial is designed to compare the efficacy of ARP and natural healing at molar extraction sites in cases with severe periodontitis. This study is expected to determine the most beneficial and least traumatic clinical treatment for such patients. The following aspects will be compared, (i) soft tissue contour and mucosa thickness change from the baseline till at least 1 year after implant loading, (ii) radiographical evaluation for vertical and horizontal change of alveolar ridge from baseline to 6 months after atraumatic tooth extraction and ARP, (iii) histological composition after 6-month healing period in /tooth extraction sites with ARP, (iv) periodontal parameter changes in the follow-up period, (v) patient-reported post-operative reaction, and (vi) finally the need of simultaneous bone graft or sinus lifting procedures during implant placement procedure.

## Methods

This research is a two-group parallel randomized controlled trial (RCT) to provide soft tissue contour, radiographical, and histological evaluation of the efficacy of ARP in 70 molar extraction sites with severe periodontitis. Figure 1 shows the framework of this trial. The design and report of this protocol follow the Standard Protocol Items: Recommendations for Interventional Trials (SPIRIT) statement [29], and the schedule of this study is shown in Fig. 2.

**Fig. 1 Fig1:**
[figure not shown]
Framework of this trial

**Fig. 2 Fig2:**
[figure not shown]
Standard Protocol Items: Recommendations for Interventional Trials (SPIRIT) Figure: schedule of enrolment, interventions and assessments. SRP: scaling and root planning; OHI: Oral hygiene instruction; ARP: Alveolar ridge preservation; CBCT: Cone beam-computed tomography; WKT: Width of keratinized tissue; PD: Probing depth; BI: Bleeding index; GR: Gingival recession

### Setting

This trial will be undertaken at the Peking University School and Hospital of Stomatology (Beijing, China). Before the trial takes place, written informed consent will be obtained from all participants.

### Participants

If a patient has unsalvageable molars as a consequence of severe periodontal disease and considers implant-retained prostheses for the extraction sockets, the patient will be suggested and reclused in this study.

The included patient should meet the following criteria:Age more than 25 yearsGood compliance and good oral hygieneDiagnosed with stage III/IV periodontitis [30]Presence of at least one hopeless molar with severe bone loss requiring extractionAt least two socket walls beyond the apex or ≥ 3 mm of the extraction socketAt least one adjacent tooth at the proximal region.

The exclusion criteria are as followed:Pregnancy or lactationPatients taking medications or having disease that would complicate bone healingPatients with surgical contraindications, such as uncontrolled hypertension or diabetes mellitusPatients with history of head and neck radiotherapySmoking more than 10 cigarettes per dayAbsence of both adjacent teethTeeth with ongoing acute pathologyTeeth extracted due to caries, endodontic failures or fractured teeth.

### Criteria for discontinuing

The exclusion criteria will be checked regularly during the study period. If the participant meets any of the exclusion criteria during the follow-up period of this study, she/he will be excluded from the study. If the participant shows poor compliance or decides to withdraw the consent due to any reason, the participation will be terminated.

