### Randomizing

A series of random numbers will be generated using Excel 2021 (Microsoft Corp., Redmond, WA, USA), written on letter paper and sealed in sequentially numbered, sealed, opaque envelopes. All the patients will be assigned to two groups by simple randomization with the rate of 1:1: the test group with alveolar ridge preservation, and the control group with natural healing. All the surgical procedures will be performed by an experienced clinician, and the other clinician will conduct the clinical examination for the patients. Another two members will take charge of intraoral scanning, assessing the radiological examinations and completing statistical analysis.

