### Blinding

Blinding is not suitable for this trial. For the participants, they can distinguish which group they are in after experiencing different surgical procedures and post-operative treatment, so can the surgeons. For the assessors, they can also differentiate two groups from different imaging manifestations.

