### Sample size calculation

The sample size was calculated using the Power Analysis and Sample Size (PASS) (version 15.0, NCSS, LLC, East Kaysville, Utah, USA) based on a two-sided alpha of 0.05 and power of 0.8. According to previous literature [13], the ridge width changes in one site (at 1 mm apically from the top of the alveolar crest in central buccal) of ridge preservation group and natural healing group were 1.46 mm and -0.70 mm, respectively. And the SD were 3.54 mm and 2.28 mm. After the calculation, the minimal sample size was 30 extraction sites for each group. Considering 15% non-response rate, 35 extraction sites will be included in this study for each group. Totally, 70 extraction sites will be needed.

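### Exclusion criteria are re-applied after randomisation and undefined poor compliance ends participation, so outcomes are lost for reasons that may be linked to prognosis

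*Protocol article*

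**What the plan says.** The Criteria for discontinuing section of the protocol article contains three linked rules.

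- Eligibility is monitored throughout: "The exclusion criteria will be checked regularly during the study period".
- A criterion met later leads to removal: "If the participant meets any of the exclusion criteria during the follow-up period of this study, she/he will be excluded from the study".
- Compliance and consent are handled together: "If the participant shows poor compliance or decides to withdraw the consent due to any reason, the participation will be terminated".

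The section does not distinguish between not performing a study procedure, stopping visits, and leaving outcome collection. It gives no definition of poor compliance and does not say who judges it.

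The Blinding section says "Blinding is not suitable for this trial" and explains that participants, surgeons and assessors can all tell the groups apart. The Statistical analysis section compares the baseline of participants lost to follow-up with that of completers, and imputes missing outcomes by K-means clustering. Neither provision mentions participants removed under the discontinuation rules.

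**The concern.** Randomisation makes the groups comparable only while everyone randomised stays in the comparison. A rule that stops measurement because of something that happens afterwards selects who contributes an outcome.

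The exclusion list in the Participants section contains several conditions that can arise after surgery: drugs or illnesses that impair bone healing, uncontrolled hypertension or diabetes, smoking above the stated daily limit, and loss of both neighbouring teeth. The first is defined by its effect on healing, which is what the trial measures. The participants have stage III/IV periodontitis. Follow-up covers about 6 months of healing, 6 months of osseointegration and at least 1 year after loading, so such events are plausible.

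The compliance clause is the more direct route to exclusions that differ between groups, because an undefined judgement is made where the assigned group is known.

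Outcomes that are not collected cannot be recovered later. An intention-to-treat statement in an analysis plan does not supply them. Imputation draws on participants who stayed and cannot restore values that are missing because healing was poor.

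**Working it through.** **Inputs from the Sample size calculation and Randomizing sections.** The calculation is "based on a two-sided alpha of 0.05 and power of 0.8". The mean ridge-width changes "of ridge preservation group and natural healing group were 1.46 mm and -0.70 mm, respectively". The spread is given as "And the SD were 3.54 mm and 2.28 mm". Allocation is 1:1, with 35 sites per group after the loss allowance.

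**Step 1. Reproduce the plan's figure.**
- Difference = 1.46 − (−0.70) = 2.16 mm.
- Sum of variances = 3.54² + 2.28² = 12.53 + 5.20 = 17.73.
- n per group = (1.960 + 0.842)² × 17.73 / 2.16² = 7.849 × 17.73 / 4.666 = 29.8, rounded up to 30, as stated.
- 30 × 1.15 = 34.5, rounded up to 35, as stated.

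The 2.16 mm difference is therefore a fair yardstick for the bias.

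**Step 2. Shift if exclusion tracks outcome perfectly (extreme case).** The three smallest of 35 standard normal values have expectations −2.107, −1.690 and −1.448. Deleting the lowest k raises the mean of the rest by the sum of their absolute values divided by (35 − k), in SD units.
- k = 2: (2.107 + 1.690) / 33 = 0.115; × 3.54 = 0.41 mm (19% of 2.16).
- k = 3: (2.107 + 1.690 + 1.448) / 32 = 0.164; × 3.54 = 0.58 mm (27% of 2.16).

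**Step 3. Shift under a partial link.** Let ρ be the correlation between the tendency to be excluded and a poor ridge outcome. Under joint normality the shift is ρ times the step 2 value. Values of 0.3 to 0.5 are assumed, because the document gives none.

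| Ridge-preservation sites lost (of 35) | ρ = 0.3 | ρ = 0.5 | ρ = 1 (extreme) |
|---|---|---|---|
| 2 | 0.12 mm (6%) | 0.20 mm (9%) | 0.41 mm (19%) |
| 3 | 0.17 mm (8%) | 0.29 mm (13%) | 0.58 mm (27%) |

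If the same losses fall in the natural-healing group instead, the SD is 2.28 mm. The shifts at ρ = 0.3 to 0.5 run from 0.3 × 0.115 × 2.28 = 0.08 mm to 0.5 × 0.164 × 2.28 = 0.19 mm. They then shrink the difference instead of enlarging it.

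**Step 4. Type I error.** This was a simulation with no true effect, 20,000 trials, 35 per group, a Welch test, and 5 sites removed from one group only.
- ρ = 0: about 0.05.
- ρ = 0.3: 0.063 (ridge preservation) or 0.062 (control).
- ρ = 0.5: 0.099 or 0.069.

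**Step 5. Power.** By a Welch calculation, power is 0.847 with 35 per group and 0.787 with 30.

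**What this illustrates.** Steps 2 to 4 assume that losses fall in one group, that removed sites are simply absent, and that outcomes are roughly normal. Ridge width is measured at 6 months, so only earlier removals affect it. Later removals affect the soft-tissue and peri-implant outcomes.

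**The case against.** The strongest defence has four parts.

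**No criterion names poor healing.** A reader might infer that the rule removes sites that heal badly, for instance through infection. The text does not support this. The acute-pathology criterion concerns the tooth to be extracted, which is gone after surgery, and the reason for extraction is likewise fixed at entry. This part stands, so the concern rests only on criteria that can arise later and on compliance.

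**Differences between groups are not shown.** A reader might infer that loss of neighbouring teeth, or new illness, will be more frequent in one group. Nothing in the document says so. Balanced exclusions would mainly cost precision and generalisability. This stands in part: the bias is possible but not demonstrated. The compliance clause remains a credible route to imbalance, although the document does not say who decides.

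**Analysis sets may sit elsewhere.** A reader might infer from the missing intention-to-treat statement that only completers will be analysed. That does not follow. A condensed article may leave analysis sets to the full protocol or analysis plan, the section concerns discontinuation, and imputation is planned. This stands, but it does not answer the problem of outcomes that are never measured.

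**Later procedures may become unsuitable.** Implant surgery and biopsy follow the randomised operation, and loss of both neighbouring teeth could prevent scan superimposition. This justifies a missing procedure or measurement. It does not justify ending all outcome collection.

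**Conclusion.** The concern holds in a limited form. The protocol article has an explicit rule that ends participation for events after randomisation. Some of those events are prognostic, and one trigger is an undefined judgement in an unblinded trial. The randomised comparison can therefore be biased.

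The size and direction cannot be determined from the document, which gives neither an exclusion rate nor a link between exclusion and outcome. The 0.12 to 0.29 mm range is an illustration for 2 or 3 losses, all in the ridge-preservation group, with an assumed correlation of 0.3 to 0.5. The 0.41 and 0.58 mm figures should not be read as the expected bias. They require exclusion to pick out exactly the worst outcomes, yet ridge change is known only once the 6-month CBCT has been superimposed on the post-operative one.

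Withdrawal of consent is a legitimate end to participation and is not part of the defect. The existing 15% loss allowance is not at fault either. It protects precision but does not remove selection.

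**What to change.** Reword the Criteria for discontinuing section so that:

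1. Exclusion criteria apply only up to randomisation.
2. Not performing a particular study procedure is separate from leaving follow-up. Where a procedure is not done, the reason is recorded and the remaining outcomes are still collected.
3. Every randomised site is followed and analysed in its assigned group unless consent for data collection is withdrawn.
4. Poor compliance is defined in advance and recorded, but does not end outcome collection.
5. The current rule is kept only to define a per-protocol set for a sensitivity analysis.

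The planned 30 and 35 sites per group do not change. The cost is a wording amendment, some follow-up of participants who would otherwise have been dropped, and slightly more outcome variability.

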### Strategies to improve adherence

All time points in this study procedure will be matched with routine maintenance visits as far as possible to ensure the adherence to this clinical trial.

### Randomizing

A series of random numbers will be generated using Excel 2021 (Microsoft Corp., Redmond, WA, USA), written on letter paper and sealed in sequentially numbered, sealed, opaque envelopes. All the patients will be assigned to two groups by simple randomization with the rate of 1:1: the test group with alveolar ridge preservation, and the control group with natural healing. All the surgical procedures will be performed by an experienced clinician, and the other clinician will conduct the clinical examination for the patients. Another two members will take charge of intraoral scanning, assessing the radiological examinations and completing statistical analysis.

### Blinding

Blinding is not suitable for this trial. For the participants, they can distinguish which group they are in after experiencing different surgical procedures and post-operative treatment, so can the surgeons. For the assessors, they can also differentiate two groups from different imaging manifestations.

### Intervention

The enrolled patients will receive clinical and radiological examinations. They will receive routine scaling and root planing, and oral hygiene instruction at least 1 week before the surgery. All the patients will also receive prophylactic antibiotic medicine (Amoxicillin, 1 g or Erythromycin 300 mg if allergic to Penicillin) and anti-inflammatory drug (Ibuprofen 300 mg) 1 h prior to the surgical procedures described previously [31].

For control group:An internal bevel incision will be performed from 0.5–1.0 mm below the buccal and lingual gingival margin to the bone crest.The selected tooth will be extracted atraumatically [31].The socket will be examined carefully and debrided thoroughly (using P24G Periosteal Elevator and CL86 Lucas Surgical Curette) without damaging the socket walls.

For test group:The steps mentioned above are the same.A full thickness flap will be elevated to expose 2 mm of the bone crest.The socket will be filled with DBBM (Bio-Oss, Geistlich Pharma AG, Wolhusen, Switzerland), and a resorbable membrane (Bio-Gide, Geistlich Pharma AG, Wolhusen, Switzerland) will be used to cover the socket completely with 2 mm extending over the crest.Then the socket will be covered by collagen sponge (Wuxi Biot Biology Technology Co.,Ltd., Wuxi, China).A cross-mattress tension-free 5–0 suture will be placed over the site.

After the surgical procedures, patients will be prescribed to take the antibiotic three times daily for 7 days and ibuprofen (300 mg twice daily for 3–5 days) if needed. Patients will be required to perform regular tooth brushing in the rest of the mouth and oral rinse with 0.12% chlorhexidine solution for the 4-week post-surgery. The sutures will be removed 2 weeks after the surgery, and all the patients will be recalled at 4 weeks after the surgical to evaluate the healing status of the surgery site.

During the whole follow-up period from baseline to the last appointment, all the participants will receive regular maintenance therapy.

### Outcome measures

#### 
Baseline examination (Fig. 
*3*
)

**Fig. 3 Fig3:**
[figure not shown]
Flowchart of data collection during follow-up period

At baseline (before tooth extraction), the following data will be collected:Full-mouth peri-apical films,CBCT images (CBCT 1): CBCT images will be taken by CBCT machines (NewTom VG; Aperio Services, Italy) at a resolution of 0.125 mm with field of view size 10 × 10 cm (exposure time: 3.6 s, 110 kV, 5 mA). It will be used for assessing anatomical conditions, including the degree of bone loss and the position of maxillary sinus/mandibular canal.Stereolithography (STL) files (STL 1): intraoral scans will be taken using a TRIOS intraoral scanner (3Shape TRIOS Color, TRC, 3Shape, Denmark) to obtain a digital impression of the target area and generate an STL file, which include the selected tooth and relevant quadrant. Soft tissues contained in this digital impression will extend over the mucogingival junction.Periodontal parameters: the periodontal conditions of the ailing tooth and adjacent teeth will be assessed by measuring probing depth (PD), gingival recession (GR) and bleeding index (BI). The width of keratinized tissue (WKT) will be measured at mid-buccal aspect from the mucogingival junction to the gingival margin of the teeth. Data will be round down to the nearest 0.5 mm, and they will be collected using an UNC-15 probe (Hu-Friedy, Chicago, IL, USA).

#### 
Examination immediately after the intervention for both groups (Fig. 3)

CBCT images (CBCT 2): it will be used for superimposition and measurement. And it will be illustrated in informed consent.STL files (STL 2)

#### 
Examinations during the follow-ups before implant therapy (Fig. 3)

STL files (STL 3–6): the patients will be recalled at 2, 4, 12 weeks and 6 months after the surgery, and intraoral scans will be performed.CBCT images (CBCT 3): CBCT examination will be performed 6 months after the surgery.Post-operative reaction: the patients will be recalled at 1, 2 and 4 weeks after the surgery to report post-operative reaction, such as pain, erythema, swelling and paranesthesia.Paralleling technique films: films will be taken 6 months after the surgery.Periodontal parameters: at 6 months after the surgery, the periodontal examination indicators (PD, GR, BI and WKT) will be recorded for the adjacent teeth, and WKT of extraction area will also be measured at the buccal aspect from the central of the (expected) implant position to the buccal mucogingival junction [32].

#### 
Examination during implant therapy (Fig. 3)

The implant therapy will be performed around 6 months after ARP/tooth extraction.Bone biopsy: during the implant placement procedure, a cylindrical bone block with a diameter of about 2 mm and length of about 5 mm will be taken out using a trephine drill (Institute Straumann AG, Basel, Switzerland). The block will be fixated in 4% formaldehyde solution at room temperature for at least one day. Then, they will receive decalcification for 3 weeks in 4.1% disodium ethylene-diamino-tetra-acetic acid-solution, the solution will be changed every 24 h. After hydration, they will be dehydrated in increasing concentrations of ethanol (from 70 to 100%), embedded in paraffin, and cut into sections with a thickness of 4 µm. Serial sagittal sections will be stained with hematoxylin–eosin. Representative regions of interest (ROIs) will be localized in the center, apically and coronally of the sample [33]. Histologic slides will be observed under light microscopes and digital images will be obtained by scanning at a magnification of × 200 for subsequent histomorphometric analysis. For the two groups, the histological composition in terms of new bone formation, residual graft particles and connective tissue will be evaluated and compared.Simultaneous bone graft & sinus lifting procedures: the conditions of bone grafting and sinus lifting during implant therapy will be recorded.

#### 
Examination during the follow-ups after implant restoration (Fig. 3)

After 6-month period of osseointegration, the superstructures will be connected to the implants. Participants will be recalled at immediately, 1-, 3-, and 6-month and then every 6 months after implant loading. During this period, the following data will be collected:STL files (STL R1, R2, and so on): intraoral scans will be performed at every appointment.Periodontal parameters: the periodontal examination indicators (PD, GR, BI and WKT) will be recorded for the implant and adjacent teeth at every appointment.Paralleling technique films: the films will be collected immediately and every 6 months after implant loading, and they will be used to evaluate the marginal bone loss (MBL).

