**Methods:**

This research is designed as a two-group parallel randomized controlled trial. The total number of tooth extraction sites will be 70 after calculation with power analysis. Teeth will be randomly assigned to two groups with the test group conducting ridge preservation and the control group healing naturally. Periodontal examination, cone beam-computed tomography (CBCT) data, and stereolithographic (STL) files obtained by intraoral scanning will be collected through the follow-up period, and bone biopsy samples would be obtained during implant surgery. The primary outcomes are the vertical and horizontal change of alveolar ridge measured on CBCT images, soft tissue contour changes evaluated by superimposing the digital impressions, alterations of mucosa thickness (as measured by superimposing the CBCT data and STL files), histological features of implant sites and periodontal parameter changes. The secondary outcomes are patient-reported post-operative reaction and conditions of simultaneous bone graft or sinus lifting procedures during implantation.

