According to Avila-Ortiz et al. [34], peri-implant phenotype is crucial to peri-implant health, function, and esthetics. Soft tissues take over an important position in the components of peri-implant phenotype. The use of intraoral scan allows to record the profile of soft tissues without any pressure. It can be used immediately after surgical procedures without disrupting the wound. Digital scanned data make it possible to measure the dimensional changes at different time points in a long-term follow-up period [26]. Up to now, only a few studies reported the three-dimensional profilometric changes on the soft tissue level based on intraoral scanned data following tooth extraction and ARP [24–26]. In the esthetic zone of single extraction sites, Chappuis et al. [24] investigated the interplay between the soft tissue morphology and the underlying bone anatomy during an 8-week healing period by sequential digitized impressions and CBCT images. Wongpairojpanich et al. [26] used intraoral scanner for monitoring the wound closure and surface dimensional changes of alveolar ridge at different time points (1, 3, 7, 14, and 28 days and 4 months after ARP). Song et al. [25] explored the changes of soft tissue dimensions following alveolar ridge preservation and spontaneous healing in posterior maxilla using intraoral scanned data and CBCT data in a 6-month healing period. To summarize, the follow-up time for current studies was relatively short. And to the best of our knowledge, there has not been specific evidence available to identify the soft tissue contour changes of ridge preservation on molar extraction sockets with periodontal pathosis before tooth extraction.

DBBM is a type of bone substitute material widely used in dental practice [35]. A systematic review included five studies showed that ridge preservation using DBBM had a lower amount of new bone formation in comparison with natural healing, but due to the lack of randomized controlled trials, limited sample size and high heterogeneity, further experiments are needed to verify this conclusion [28]. Koo et al. [36] carried out a histological analysis at 4-month after ARP in damaged extraction sites, showing a low mean proportion of regenerated bone and a large variation from 0 to 43%. Further studies with longer healing time in periodontally compromised sockets are needed for evaluating the histological changes of ridge preservation.

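### Histology is a primary outcome, but the field scored within each zone of the core is chosen as representative, a judgement open to someone likely to know the arm

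*Protocol article*

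**What the plan says.** The abstract's list of primary outcomes includes "histological features of implant sites and periodontal parameter changes". Under Examination during implant therapy, the specimen is "a cylindrical bone block with a diameter of about 2 mm and length of about 5 mm". Fields are chosen as follows: "Representative regions of interest (ROIs) will be localized in the center, apically and coronally of the sample", with a reference to a published method. The slides are then digitised: "digital images will be obtained by scanning at a magnification of × 200 for subsequent histomorphometric analysis". Between the groups, "the histological composition in terms of new bone formation, residual graft particles and connective tissue will be evaluated and compared".

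The Blinding section opens with "Blinding is not suitable for this trial" and extends this to assessors, on the ground that imaging shows the group. The Randomizing section assigns surgery, clinical examination, intraoral scanning, radiology and statistics to team members. It names no histology reader. Under Intervention, only the test group has bone substitute placed in the socket at extraction.

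**The concern.** A field called representative is picked after someone has looked at the section. What is looked at (bone, graft particles, connective tissue) is the outcome itself. The choice can therefore follow what the chooser expects to see, even without intent.

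Masking is a weak remedy here. Residual graft is one of the three scored components, and only the test group receives graft at extraction, so even coded slides would often give the arm away. An expectation is also available: Background and Discussion both report that this substitute gave less new bone than natural healing in earlier work. A lean in either direction is possible.

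At stake is the between-group comparison of tissue composition. The Discussion says this comparison lacks good randomised evidence.

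**Working it through.** **1. What is fixed and what is open**

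| Item | Article |
|---|---|
| Zones | Fixed: centre, apical, coronal |
| Criterion within a zone | Representative |
| Field size, number and position within a zone | Not given; a cited method may cover them |
| Who chooses the fields | Not stated |
| Blinding | Disclaimed for the trial, assessors included |
| Extent of scan | ×200; whole section or fields only not stated |

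The only selection criterion that the article states depends on the tissue.

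**2. The plan's own figure.** The sample size rests on CBCT ridge width, not histology. The difference is 1.46 − (−0.70) = 2.16 mm and the mean variance is (3.54² + 2.28²)/2 = 8.865. Then n = 2 × (1.960 + 0.842)² × 8.865 / 2.16² ≈ 29.8, or 30 per group, as stated. It says nothing about histology, which has no stated effect or SD. It only supplies a group size for step 5.

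**3. Share of the section seen.** The mid-section is about 2 × 5 = 10 mm². Field size is not given. For three square fields of assumed side s, coverage is 3s²/10:
- s = 0.5 mm: 7.5%
- s = 0.75 mm: 16.9%
- s = 1.0 mm: 30%

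**4. Shift from selective choice (illustration).** Let fields within a zone vary with SD w. The article gives no value; assume w = 5 to 10 percentage points. If the highest of k candidates is always taken, the expected shift is c × w, with c = 0.564 for k = 2 and 0.846 for k = 3.

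| | w = 5 | w = 10 |
|---|---|---|
| k = 2 | 2.8 | 5.6 |
| k = 3 | 4.2 | 8.5 |

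Averaging three zones leaves the shift unchanged if all three lean the same way. If only one leans, it falls to a third (0.9 to 2.8 points). If the chosen fields are truly typical, it is zero.

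**5. Effect on the test (illustration).** Take 30 per group, no true difference, and a shift in one arm only. Assume a between-site SD of 10 to 15 points. For context, one cited study is described as "showing a low mean proportion of regenerated bone and a large variation from 0 to 43" per cent across sites; a rough range/4 rule gives 43/4 ≈ 11. The standard error is SD × √(2/30), which is 2.58 or 3.87 points. The rejection rate comes from a noncentral t with 58 degrees of freedom and noncentrality shift/SE, at two-sided 5%.

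| Shift in one arm | SD 10 | SD 15 |
|---|---|---|
| 2 points | 12% | 8% |
| 5 points | 48% | 25% |

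So even a modest one-sided lean could matter, but nothing in the article shows that one will occur.

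**The case against.** The strongest reply is that this is laboratory detail which a condensed article leaves to the full protocol and to the cited method. Coronal, central and apical sampling is already a defined scheme, and whole-section scoring is merely an alternative. That stands as far as field size and number go; their absence is not held against the article. It does not cover the criterion that the article does state, which depends on the tissue being scored.

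A reader might also infer more than the text supports:

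- **That the histology reader is known to be unblinded.** No such reader is named, and the reason given for assessors is imaging, not slides. Knowledge of the arm is a fair inference from the general disclaimer and the visible graft, not a stated fact.
- **That the reader may choose anywhere.** The zones are fixed, so only the choice within a zone is open.
- **That scoring is confined to these fields and the whole section is already scanned.** The first is implied and the second is not stated.
- **That the bias has a known size.** The within-zone spread has no source in the article. The 0 to 43% range is between sites, not within a core. Taking the highest field every time models deliberate selection, not an honest search for a typical field. Doubling the shift by assuming opposite leans in the two arms has no support either.

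Scoring only the part of the core inside the former socket would not solve the problem. Drawing that boundary after six months is another judgement, and graft particles could guide it in one arm only.

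**Conclusion.** The point holds as a cheap improvement to the measurement of one of several primary outcomes. Within each zone, the stated criterion leaves the field to judgement, probably by someone who can tell the arm. That last step is inferred from the Blinding section and from graft being visible and scored.

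Neither size nor direction can be derived from the article. The figures of 0 to 8.5 points, and false-positive rates of 8 to 48% for one-arm shifts of 2 to 5 points, rest wholly on assumed spreads and selection behaviour. They show why the choice deserves a rule, not that the result will be biased. The sample size is not affected.

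**What to change.** Keep the three zones and drop representative as the selection criterion. State a field size, and place the fields at pre-set distances from the coronal end along the core axis, before any tissue is classified and with no re-selection. Alternatively, score the entire core section without drawing a former-socket boundary.

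Both rules work whether or not the reader recognises the arm. Neither removes judgement in telling new bone from residual graft, which is a separate matter.

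The cost is a wording change and some extra image-analysis time, plus whole-section scanning if only the fields were to be scanned. No extra biopsy or reader is needed.
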